**Matching variables for propensity score**		
Prenatal attachment (Prenatal Attachment Inventory)	Continuous	[10, 11, 41]
Prenatal Depression (PHQ-9)	Continuous	[10, 11, 41, 42]
Prenatal Anxiety (GAD-7)	Continuous	As above
Ethnicity	Categorical	[10, 11, 30, 41, 43]
Socioeconomic position (financial security)	Continuous	[30, 42, 44–46]
Speaks English	Binary	[30, 46]
Immigration status (proportion of life spent in UK)	Continuous	[30, 47, 48]
Length of time in COVID lockdown	Continuous	[49]
**Moderators**		
Child age	Continuous	N/A
Programme delivery mode (face to versus or virtual)	Binary	N/A
Socioeconomic position (financial security)	Continuous	N/A
Ethnicity	Categorical	N/A

Participants who entered reception prior to or during September 2020 will be assessed according to the old version (though this is anticipated to be a small number of participants), and participants in IY-T who enter reception after or during September 2021 will be assessed according to the new version. The measures will be made comparable by collapsing all participants who met or exceeded goals to be assigned a one, and each goal scored as emerging will be assigned a zero.

### Sample size calculations

This study has a fixed sample size dependent on the projects capacity and recruitment rates, and this section explores the required sample size to obtain 80% power. The EYFSP will be modelled as an ordinal outcome, using a proportional odds model. We have calculated the numbers at which we will have 80% power to detect an odds ratio of 1.5, which is thought to be equivalent to a Cohen’s *d* of .20 (small effect size) [35]. We have used an allocation ratio of 1:3 (intervention:control). The Stata command *artcat* was used for all sample size calculations.

For the primary outcome using five ELGs, we will be powered to detect a difference with 1336 participants total (334 intervention participants and 1002 control participants).For the secondary outcome using all 17 ELGs, we will be powered to detect a difference with 950 participants total (237 intervention participants and 713 control participants).

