#### Intervention

IY-T is the intervention. Parents living in the BSB area with a child aged 1–3 are eligible to enrol in IY-T. IY-T receive most of their enrolled participants through their own engagement with the community directly, and also through engaging with schools and nurseries. IY-T aim to recruit approximately 12 parents to each group that they run.

Within IY-T, parents learn how to help their toddlers feel loved and secure, encourage social and emotional development, and establish strategies for developing routines, handling separation, and managing misbehaviour [15]. Parents/carers receive 3 promotional contacts prior to the beginning of the group via assertive outreach, consisting of telephone contact and at least one home visit. The initial telephone contact introduces the parents to the project and Group Facilitators, and aims to build the participants confidence in attending. The home visits are intended to create a sense of rapport between the family and Group Facilitators and alleviate any barriers that families might have in accessing the group such as crèche, language difficulties, or concerns about what the group might involve. The intervention will be delivered in a combination of face-to-face and virtual formats (dependent on lockdown rules in place during the COVID-19 pandemic at the time of the study and participant needs) by trained Group Facilitators who receive regular supervision from an accredited IY mentor.

The 13 IY Toddler Basic sessions cover eight topics:

Part one –Child-Directed Play Promotes Positive RelationshipsPart two–Promoting Toddler’s Language with Child-Directed CoachingPart three–Social and Emotion CoachingPart four–The Art of Praise and EncouragementPart five–Spontaneous Incentives for ToddlersPart six–Handling Separations and ReunionsPart seven–Positive Discipline-Effective Limit SettingPart eight–Positive Discipline-Handling Misbehaviour

Further detail on the content and delivery of the IY-T intervention, and materials, can be found here: https://incredibleyears.com/programs/. The IY-T theory of change and logic model developed by Barnardo’s for Bradford delivery states that IY-T will result in improvements in child social and emotional development over the medium and long term. The logic model is provided in a S2 File.

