### Statistical methods

A detailed statistical analysis plan will be preregistered on the Open Science Framework (OSF), this section is provided as a summary. Our analyses will use the propensity score matching method, which estimates the probability of a subject to receive a treatment conditional on the set of covariates. Matching patients with a similar estimated propensity score will create approximate balance for baseline characteristics [36]. The propensity score method will use one-to-*many* matching, by matching individual treatment cases to multiple control cases [37]. After matched groups have been created, ordinal logistic regression analyses will be run using group assignment as the independent variable, and the primary and secondary outcomes as the dependent variables.

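### The 80% power stated at 334 + 1002 makes no stated allowance for delivery of the intervention in parent groups, so it is an upper limit rather than the expected power

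*Protocol article*

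**What the plan says.** The protocol's section on sample size calculations describes its purpose as follows: "this section explores the required sample size to obtain 80% power". The inputs given are the model ("The EYFSP will be modelled as an ordinal outcome, using a proportional odds model"), the effect ("80% power to detect an odds ratio of 1.5"), the allocation ("We have used an allocation ratio of 1:3 (intervention:control") and the software ("The Stata command *artcat* was used for all sample size calculations"). The result for the primary outcome is "we will be powered to detect a difference with 1336 participants total (334 intervention participants and 1002 control participants". For the 17-goal secondary outcome it is 950 (237 + 713). The section also says that the sample is fixed by the project's capacity and recruitment.

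The section on the intervention says "IY-T aim to recruit approximately 12 parents to each group that they run". Trained facilitators run the groups. Comparison families must never have been referred to or enrolled in the programme, so they belong to no group.

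The statistical methods section says "ordinal logistic regression analyses will be run using group assignment as the independent variable", and the software section names *ologit*. The statistical methods section describes itself as a summary of an analysis plan to be preregistered.

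**The concern.** Families in one parent group share facilitators, sessions, delivery period and format, and they influence each other. Their children's outcomes may therefore be more alike than those of families from different groups. Controls have no such structure. A two-group calculation that treats every child as independent understates the variance of the intervention arm whenever this correlation is positive.

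The intervention arm is the smaller one and dominates the variance of the comparison, so inflation there matters more than it would at 1:1. Because the sample is fixed, lost power cannot be recovered by recruiting. A reader who takes 80% at face value would read a null result as stronger evidence against an odds ratio of 1.5 than it is.

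**Working it through.** **Inputs from the protocol.** Odds ratio 1.5; 80% power; 334 + 1002 (primary) and 237 + 713 (secondary); groups of about 12 parents; not all attendees belong to the cohort.

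**Assumptions.** Two-sided 5% test (not stated in the section); ICC 0.01 to 0.05 (not stated); 4 to 6 analysed cohort families per group (not stated), with 12 as an upper bound because the delivered groups include parents outside the cohort.

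**Step 1: the plan's own figure.** The Whitehead formula for proportional odds, with A = 3 controls per intervention child, is

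N = 3(A+1)²(z₁+z₂)² / [A (ln OR)² (1 − Σp̄³)],

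where p̄ are the average category proportions. With z₁+z₂ = 1.960 + 0.842 = 2.802 and ln 1.5 = 0.405, this becomes N = 763.9 / (1 − Σp̄³).

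- N = 1336 needs 1 − Σp̄³ = 763.9/1336 = 0.572. With the other five categories equally common, this corresponds to about 73-74% of controls meeting all five goals.
- N = 950 needs 763.9/950 = 0.804. With the other categories equally common, this corresponds to about 56% of controls meeting all 17 goals.

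Both are plausible, so the figures fit a calculation without inflation. They cannot be reproduced exactly, because the category distribution is not given.

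**Step 2: weight of the intervention arm.** Its share of the variance is (1/334) / (1/334 + 1/1002) = 1002/1336 = 0.75. For the secondary outcome it is 713/950 = 0.75.

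**Step 3: variance inflation.** With m analysed families per group, the design effect applies to the intervention arm only:

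DE = 1 + (m − 1) × ICC; VI = (3 × DE + 1)/4.

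**Step 4: power at 334/1002.** Taking 80% as the value without clustering, power = Φ(2.802/√VI − 1.960). Worked case, m = 6 and ICC 0.05: DE = 1.25, VI = 4.75/4 = 1.188, √VI = 1.090, 2.802/1.090 = 2.571, and Φ(0.611) = 72.9%.

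| Analysed families per group | ICC 0.01 | ICC 0.02 | ICC 0.05 |
|---|---|---|---|
| 4 | 79.1% | 78.2% | 75.7% |
| 6 | 78.5% | 77.1% | 72.9% |
| 12 (upper bound) | 76.8% | 73.7% | 65.4% |

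The intervention share is 0.75 for both outcomes, so the same percentages apply at 237/713 if the ICC is the same.

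**Step 5: the loss as a sample size.** The total for 80% power at 1:3 is 1336 × VI. At ICC 0.05 it is 1487 for m = 4, 1587 for m = 6 and 1888 for m = 12. These totals only show scale, since enrolment is fixed.

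**The case against.** The strongest reply is that the size of the loss is unknown. No ICC is given, and the outcome is recorded two to four years after the programme. Analysed groups are smaller than 12. The intention-to-treat set includes enrolled families who never took part and so share no group experience. At the low end of the table the loss is one to two points. A fixed sample also means that a revised total changes no recruitment. All of this stands, and it is why the result is a range and why 65% is not the expected figure. It does not restore 80%, because every positive ICC moves power the same way. An inflation hidden in 1336 cannot be strictly excluded, but none is stated.

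A second reply is that variance estimation belongs to the analysis plan. That is right for the model but does not reach the power figure: the deferral stands in the statistical methods section, while the sample size section gives a definite number.

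A reader might infer three stronger points that the protocol does not support.

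- **That the planned intervals are too narrow and the test rejects too often.** This would follow only from default standard errors. A summary that names *ologit* does not commit to them, since the command also accepts clustered ones. Moreover, if the programme affected no child, shared delivery would create no correlation, and only similarity in group composition would remain.
- **That group size can be derived from the 54% recruitment figure.** That figure is cohort uptake in the eligible pregnant population, not the cohort's share of programme attendees.
- **That a school effect is required because teachers rate the outcome.** Both arms come from the same three areas. Where schools contain children from both arms, ignoring school need not make standard errors too small.

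**Conclusion.** The point holds for the power statement. The protocol presents 80% power at 334/1002 with no stated allowance for a group-delivered intervention arm, and any positive within-group correlation makes that figure too high. For 4 to 6 analysed families per group, the loss is about 1 to 2 points at ICC 0.01, 2 to 3 at 0.02 and 4 to 7 at 0.05. It is about 15 points in the upper-bound case of 12 per group at ICC 0.05. These sizes rest on an assumed ICC and group size, a two-sided 5% test, and 80% being the value without clustering. Non-attenders in the intention-to-treat set would make the loss smaller. Completers in the per-protocol set all attended sessions, so that dilution does not apply to them.

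For the analysis, the conclusion is conditional: default standard errors would be too small if outcomes correlate within groups. Whether they will be used cannot be settled from this document.

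**What to change.** 1. State the assumed ICC and its range, and the observed number of cohort families per parent group. Restate power at 334/1002, and at 237/713 for the secondary outcome, as a range under the partially nested design.
2. State in the analysis plan that the ordinal model uses standard errors clustered on parent group in the intervention arm, with controls and enrolled families who never joined a group as their own clusters. A random effect for parent group in the intervention arm only is the alternative.

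The cost is a few lines of text and slightly less favourable stated power. A pseudonymised group identifier must also be carried into the analysis file. The protocol says that data are anonymised before researchers receive them, so this identifier has to be requested. No additional families are needed.

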### Data timeline

This study will use all available data since IY-T began (1^st^ September 2018) up until the end of their service delivery period (expected to be 30^th^ April 2024). Fig 1 provides the participant pathway through BiBBS cohort recruitment, participation in IY-T (or non-participation), and school entry with the outcome collected during reception year. Parents may enrol in the intervention when their child is aged anywhere between 1 and 3 years old, which means outcome data may be collected anywhere between two and four years after intervention participation. The routine education outcome in the EYFSP, which is reported by teachers at the end of children’s reception year in primary school (when child is aged 5 years old, equivalent to 60 months). The final analyses will be after August 2028, when the youngest children within the delivery period reach age 5 years.

**Fig 1 pone.0291557.g001:**
[figure not shown]
Overview of timeline of participation and data collection. Note: Caregivers are eligible for IY-T when their child is aged 12–36 months old. Participation in the IY-T programme lasts approximately 12 weeks.

### Statistical methods

A detailed statistical analysis plan will be preregistered on the Open Science Framework (OSF), this section is provided as a summary. Our analyses will use the propensity score matching method, which estimates the probability of a subject to receive a treatment conditional on the set of covariates. Matching patients with a similar estimated propensity score will create approximate balance for baseline characteristics [36]. The propensity score method will use one-to-*many* matching, by matching individual treatment cases to multiple control cases [37]. After matched groups have been created, ordinal logistic regression analyses will be run using group assignment as the independent variable, and the primary and secondary outcomes as the dependent variables.

### Variables

The Directed Acyclic Graph (DAG) in Fig 2 identifies the confounding variables that will be used as matching variables in the propensity score [38, 39]. We will match on the 7 characteristics on the left-hand side of the graph (prenatal attachment, prenatal depression, prenatal anxiety, ethnicity, socioeconomic status, language status, and immigration status) to estimate the effect of treatment (IY-T) on the primary outcome (child social and emotional development).

**Fig 2 pone.0291557.g002:**
[figure not shown]
Directed Acyclic Graph of associations between confounders, covariates, moderators, treatment exposure, and outcome. Notes: 1. SES = socioeconomic status. 2. The secondary outcome (children’s early years school skills) is not depicted here.

The justification for the selection of these variables is given in Table 2 below. Variables which affect program participation but not the outcomes should not be used in propensity score matching, as this increases the error in the estimated values [40]. Matching variables were therefore selected if they were thought to have an association with both uptake of treatment, and with the outcomes (child early years development), and there was evidence to suggest this was the case. See Table 2 for a summary of the evidence for using a matching variable, and the tested moderators of the effect. We have proposed that we will test the effects of four moderators: child age, programme delivery mode, family socioeconomic status, and ethnicity, however, this will only be possible if a sufficient sample size is reached.

All variables are obtained from the BiBBS baseline questionnaire, which takes place before the child is born (see https://borninbradford.github.io/datadict/bibbs/ for details).

### Included participants

We will conduct both Intention to Treat (ITT) analyses to ascertain the effects of enrolling in the intervention [50, 51], and per protocol analyses to ascertain the effects of receiving the treatment [52]. The ITT analyses will therefore include all who enrolled in the intervention after an initial home visit (even if they did not go on to participate in it), and the per protocol analyses will only include ‘completers’, defined as those who take part in at least 8 out of the 13 sessions. This will give us more accurate estimates of the average treatment effect on the treated participants.

Parents are eligible for the evaluation regardless of whether they are the mother, father, or another type of co-parent. Whilst we anticipate that the majority of parents in this study will be mothers, we will describe the number of fathers and other co-parents if possible.

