### Design

This effectiveness evaluation will use a quasi-experimental design. A quasi-experimental design lacks random assignment and uses self-selection (by which participants choose treatment or a lack of treatment for themselves) [26]. The analyses will use propensity score matching, where multiple control cases will be matched to intervention cases (see statistical methods for further details).

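### Restricting the per protocol analysis to completers does not make the estimated effect on the treated more accurate; it changes the target group and adds one-sided selection on attendance

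*Protocol article*

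**What the plan says.** The Included participants section of the protocol article sets out two analyses.

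- The intention-to-treat analysis is to "include all who enrolled in the intervention after an initial home visit (even if they did not go on to participate in it").
- The other is described as "per protocol analyses to ascertain the effects of receiving the treatment"; in it, "the per protocol analyses will only include ‘completers’, defined as those who take part in at least 8 out of the 13 sessions".

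The paragraph closes with "This will give us more accurate estimates of the average treatment effect on the treated participants".

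Four other places bear on this claim:

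- **Design:** "A quasi-experimental design lacks random assignment and uses self-selection".
- **Eligibility criteria:** a comparison parent must never have been referred to or enrolled in the programme.
- **Variables:** the matching set is "prenatal attachment, prenatal depression, prenatal anxiety, ethnicity, socioeconomic status, language status, and immigration status". The variables were chosen because they were thought to be associated with both uptake and outcome. The text after Fig 2 adds: "All variables are obtained from the BiBBS baseline questionnaire, which takes place before the child is born". Table 2 lists one further matching variable, time in COVID lockdown.
- **Study limitations:** selection on attendance is not mentioned.

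**The concern.** In a self-selected design, the credibility of a contrast rests on the matching set. That set was built for one selection step, from not enrolling to enrolling. The completer analysis adds a second step, from enrolling to attending eight or more sessions, and only the intervention side can be filtered. Families who persist may differ from those who drop out in motivation, stability or the child's behaviour after birth. No matching variable measures these directly at the time attendance is decided.

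What is at stake is how the results are read when the two analyses disagree. Suppose the enrolment analysis is null and the completer analysis positive. A reader who takes the closing sentence at face value would prefer the completer odds ratio as the more accurate one, although selection alone could have produced the difference.

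**Working it through.** **1. What each analysis targets.** In a matched comparison in which controls are found for the intervention cases, the target is the effect in the intervention cases supplied.

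- *All enrolled:* the effect of enrolling, among those who enrolled. This is already an effect on the treated, with treatment defined as enrolment.
- *Completers:* the effect of receiving the sessions, among those who attended 8 or more. This is a different group and a different definition of treatment, so it is not a sharper estimate of the first quantity.

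**2. The condition the completer analysis needs.** Controls have no attendance status, so would-be completers among them cannot be identified. The contrast is unbiased only if, given the matching variables, completion is unrelated to the outcome the child would have had without the programme. The enrolment contrast needs the corresponding condition for uptake, and the variables were chosen with that one in mind.

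**3. Size under assumed values.** The document gives no completion rate and no attendance–outcome association, so everything in this step is illustrative. Let *u* be an unmeasured standard-normal trait. Assume no true effect and perfect balance between enrolled families and controls.

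- Completion: P(complete | u) = expit(k + g·u), with k set to give the assumed completion rate.
- Outcome: P(top category | u) = expit(a + b·u), with a set so that 74% of controls are in the top category (assumed).
- Completer proportion: p = E[P(top | u)·P(complete | u)] / P(complete).
- Odds ratio: OR = [p/(1 − p)] / [0.74/0.26].

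| b (outcome) | g (completion) | Completing | p | OR | ln OR / ln 1.5 |
|---|---|---|---|---|---|
| 0.3 | 0.5 | 70% | 0.748 | 1.044 | 11% |
| 0.5 | 0.7 | 60% | 0.764 | 1.135 | 31% |
| 0.7 | 1.0 | 50% | 0.791 | 1.332 | 71% |
| −0.3 | 0.5 | 70% | 0.732 | 0.96 | −10% |
| −0.7 | 1.0 | 50% | 0.689 | 0.78 | −62% |

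The negative rows describe the case where the trait that keeps a family attending goes with a poorer outcome, for example a child who is harder to manage.

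**4. Cross-check with the planned model.** A separate simulation fitted an ordinal logit adjusted for a measured covariate. The true OR was 1, enrolment depended on the measured covariate only, and completion depended on that covariate and on *u*, with b of 0.3 to 0.5 and g of 0.7 to 1.0.

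| Completing | Completer OR |
|---|---|
| 40% | 1.15 to 1.25 |
| 60% | 1.06 to 1.18 |
| 80% | 1.04 to 1.12 |

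The enrolment OR stayed at 0.97 to 1.05, which is simulation noise. With b = 0 the completer OR was 0.98 to 1.02, so the shift comes from the link between completion and outcome.

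**5. Precision.** The completer set is also smaller. The only related figure in the plan is the primary sample size of 1336 (334 + 1002) for OR 1.5 and 80% power. Whitehead's formula, with two-sided alpha 0.05 (assumed), gives N = 763.9/(1 − Σpᵢ³). The category distribution is not stated, so 1336 cannot be reproduced exactly. It implies 1 − Σpᵢ³ = 763.9/1336 = 0.572, or about 75% in the top category if the rest are even, which is plausible and close to the 74% assumed above.

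If 334 enrol and three controls are kept per completer, power for OR 1.5 falls from 80% to about 71%, 58% and 42% at 80%, 60% and 40% completion. So the completer estimate is less precise too.

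**The case against.** **Completers are a legitimate target.** The section separates the effect of enrolling from the effect of receiving treatment. If treatment means receiving the sessions, completers are the treated. This stands. A reader might infer that the completer analysis estimates no effect on the treated at all; the document does not support that. What fails is the claim of greater accuracy, which needs an unstated assumption.

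**The subject of the closing sentence is ambiguous.** It may refer to running both analyses rather than to the completer restriction. That is possible, but neither reading gives grounds for greater accuracy.

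**The matching set may capture part of persistence.** Prenatal attachment, depression, anxiety and financial security are plausible partial proxies, and lockdown time can hardly be purely prenatal. This stands. Matching completers on these variables would remove the measured part, and only the remainder is at issue.

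**The bias need not be upward.** A reader might infer that the completer odds ratio will be inflated. The document gives neither sign nor size, and the reversed-sign rows above are equally compatible with it.

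**Much of this belongs in the analysis plan.** The Statistical methods section describes itself as a summary and promises a detailed plan. Intention-to-treat is listed first, and nothing says that the completer result will carry the conclusion. A reader should not infer that it has been made primary. A supplementary per protocol analysis is ordinary practice. The objection does not reach the accuracy claim, which this document makes outright.

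**Conclusion.** The point holds as a fault in what the protocol claims, not in having a per protocol analysis. The completer comparison addresses a different group from the enrolment comparison, filters one side on behaviour after enrolment, and relies on matching variables chosen for uptake and outcome rather than attendance. It is unbiased only if completion is unrelated to the outcome given those variables.

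Under the assumed trait strengths, a 74% top category and no true effect, selection alone gives a completer OR between about 1.04 and 1.33, or between about 0.96 and 0.78 with the sign reversed. Against a planned OR of 1.5, the upper end is not negligible. These ranges show what is possible; they do not predict the bias in this study. The cross-check treats the enrolment contrast as free of unmeasured confounding, which isolates the attendance step but is itself an assumption in a self-selected design.

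**What to change.** 1. Delete the closing sentence of Included participants, or reword it to say that the two analyses address different questions: enrolling, among enrolled families, and receiving at least 8 sessions, among completers.
2. State that the enrolment (intention-to-treat) analysis carries the conclusion.
3. For the completer comparison, re-estimate the propensity score, re-match, and report balance for that group.
4. Label it supportive and state its assumption of no unmeasured confounding of attendance. Ideally add a sensitivity analysis showing how strong an unmeasured driver of completion would have to be to explain the result.

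Dividing the enrolment effect by the proportion completing is a tempting alternative and should not be adopted. Enrolment is self-selected here, so the division also magnifies any residual enrolment confounding (doubling it at 50% completion). It further assumes no benefit for non-completers, who may have attended up to 7 sessions and had outreach with at least one home visit.

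The cost is a change of wording, one further matching run and, if adopted, one sensitivity analysis. The downside is a more cautious reading of the completer result. Final analyses are planned for after August 2028, so there is time.
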